#### Data processing

Clinical data will be collected at the individual hospital centres using, where necessary, hospital-based records and hardcopy CRF forms. These clinical data will then be input into the eTHoS database by local researchers using an electronic web-based data capture system (in addition, relevant clinical data will be collected from routine data sources (HES, PEDW & ISD)). Extensive range and consistency checks will enhance the quality of the data. Staff in the Study Office will provide periodic data queries to local research staff to ensure that the data are as complete and accurate as possible.

### Analysis plans

The full details of the statistical analysis plan (SAP) can be obtained from the Trial Office by contacting [contact].

#### Ground rules for the statistical analysis

Study analyses will follow the SAP agreed in advance by the Trial Steering Committee. The main statistical analyses will be based on all participants as randomised, irrespective of subsequent compliance with the treatment allocation.

The primary outcome, area under the curve (measured by EQ-5D), will be generated for each participant using the trapezoidal rule. Missing EQ-5D data will be estimated using a multiple imputation approach which makes use of partial outcome data [14]. Sensitivity analyses will be conducted to assess the robustness of the treatment effect estimate to these approaches. The primary outcome measure will be analysed using linear regression with adjustment for the minimisation variables. Secondary outcomes will be analysed using generalised linear models with adjustment for minimisation and baseline variables as appropriate. Statistical significance will be at the two-sided 5% level with corresponding confidence intervals derived. Subgroup analyses will explore the possible treatment effect modification of clinically important factors (grade and gender), through the use of treatment by factor interaction, all using a stricter two-sided 1% level of statistical significance.

An independent Data Monitoring Committee (DMC) will meet early in the course of the trial to agree to its terms of reference and will review confidential interim analyses of accumulating data.

#### Timing and frequency of analyses

A single principal analysis is anticipated once the final participant has reached the 24 months time point. The DMC will determine the frequency of confidential interim analyses. The potential for analysing longer-term follow-up data (post 24 months) will be assessed once the principal analysis has been carried out.

#### Planned subgroup analyses

Subgroup analyses are planned to investigate the influence of haemorrhoidal grade and gender.

#### Economic analysis

##### Costs of management of haemorrhoids for eTHoS participants

Participant costs will comprise three main elements: self purchased health care, travel costs for making return visit(s) to NHS health care, and time costs of travelling and attending NHS health care.

Self-purchased health care is likely to include items such as prescription costs and over-the-counter medications. Information about these will be collected through the healthcare utilisation questions.

Estimation of travel costs requires information from participants about the number of visits to, for example, their GP or consultant (estimated from the healthcare utilisation questions) and the unit cost of making a return journey to each type of healthcare provider (from the Participant Unit Cost Questionnaire).

The cost of participant time will be estimated in a similar manner. The participant will be asked, in the Participant Unit Cost Questionnaire, how long they spent travelling to and attending their last visit to each type of healthcare provider. Participants will also be asked what activity they would have been undertaking (for example, paid work, leisure, or housework) had they not attended the healthcare provider. These data will be presented in their natural units (for example, hours) and also as cost estimates using standard economic conventions (for example, the Department of Transport estimates for the value of leisure time). These unit time costs, measured in terms of their natural and monetary terms, will then be combined with estimates of the number of healthcare contacts derived from the healthcare utilisation questions.

##### Costs of intervention

The costs of the surgical interventions will be recorded on a per patient basis. The resources used to provide surgery will be calculated by consulting with relevant staff (surgeons, theatre nurses, business managers) and members of the trial team to elicit information on the following:reusable equipment,frequency of use of that equipment,consumables used during surgery,staff mix of the surgical team andoverheads costs for specific time periods.

In addition to this, the operative details will be collected on the CRFs and will provide estimates of the grade of operator, assistant and anesthetist, as well as relevant procedure times.

Unit costs for these resources will be based on nationally available data and study-specific estimates. Longer term estimates of resource use and cost will be derived from trial estimates and the literature.

Length of stay information will be elicited for each patient through the case report forms by collecting the date of admission and discharge. Unit costs for each level of care will be initially obtained from the Scottish Health Service Costs (SHSC) [15] for the primary analysis and NHS National Reference Costs in a secondary analysis. These sources will not have a cost per day for all hospital services; therefore some calculations will be needed to determine the ‘cost per day’ for each level of care.

##### Costs of subsequent care

The number of outpatient visits per patient for each relevant specialty will be obtained from the CRFs. Unit costs for outpatient visits will initially be obtained from the SHSC [15] for the primary analysis and National Reference Costs in the sensitivity analysis [16].

The number of general practice contacts, for example GP office or home visits or phone consultations, will be obtained from the Health Service Utilisation Questionnaire. Unit costs for GP visits will be obtained from the Personal Social Services Research Unit (PSSRU) unit costs of community care [16]. For each patient, the number of visits will be multiplied by the appropriate unit cost. These costs will be summed to produce a total cost per patient. When a cost for each patient has been estimated, a mean cost for each intervention group will be calculated.

Any reoperations or new surgical interventions will be identified from the CRFs and for the associated cost estimated using data from routine data sources [15, 16] or operation costs previously estimated for the study. Any duration of any relevant admissions during the follow-up period will be estimated from the CRFs and the associated cost estimated using the methods described above.

##### Cost effectiveness

As part of this study, an economic evaluation will be conducted. It will be based on both a modelling exercise and a ‘within trial’ analysis. Either an existing, or *de novo,* economic model will be used to assess the relative cost-effectiveness (assessed in terms of incremental cost per QALY) and net benefits of SH and TH. A model was developed as part of a recent HTA-funded project, and we have negotiated access to that model [6]. Our group has also developed a model to compare the cost-effectiveness of SH and RBL for grade II haemorrhoids. We will critique these models and use, or adapt them, to address our study question. If necessary we will use the lessons learnt from these models to develop a new model that better addresses the research question. The data from the trial will be the main source of data for the modelling but further data with which to model outcomes beyond a 24-month follow-up will be systematically derived from the literature and other existing data sources following guidance for best practice [17].

Data collection from the trial will focus on estimating the use of secondary and primary care resource use and on health state valuations obtained from EQ-5D. Resource use and patient costs will be obtained from participant-completed questionnaires at 12 and 24 months. Unit cost will be based on nationally available data and study-specific estimates. Longer term estimates of resource use and cost will be derived from trial estimates and a structured review of the literature. QALYs will be estimated from the responses to the EQ-5D valued using the UK population tariffs.

The results of the economic model will be supplemented by a within-trial analysis. This analysis will use the estimates of costs and QALYs estimated for each trial participant to calculate the incremental cost-effectiveness ratios for the 24-month follow-up, and where appropriate, the analysis will mirror the statistical analysis (for example, incremental costs and QALYs will be adjusted for the minimisation variables using regression techniques). To facilitate interpretation of the trial results, the within-trial economic analysis will also be presented in the form of a balance sheet where differences in terms of benefits and costs of the two trial interventions are presented in their natural or clinical units.

The perspective of the model and within-trial analyses will be the patient and the UK NHS. The results of the analyses will be presented as point estimates of mean incremental costs, effects and incremental cost per QALY. Sensitivity analysis will be applied to the model in order to assess robustness of the results to realistic variations in the levels of the underlying data and also alternative assumptions, for example, QALYs derived from the SF-36. This will be accomplished using probabilistic and deterministic sensitivity analyses to address parameter and other forms of uncertainty. Similarly, for the within-trial analysis, techniques such as bootstrapping will be used alongside deterministic sensitivity analyses to address uncertainty. In both the model and the within trial analyses the cost per QALY data will be presented in terms of cost-effectiveness acceptability curves (CEACs).

##### Discrete Choice Experiment analysis

The results of the DCE will be combined with the clinical outcomes estimated from the trial or model to provide an estimate of the mean WTP for each intervention considered for both the model based and the within trial analyses. Results will be presented as incremental net benefits (Net benefits = mean WTP - mean cost for each intervention). The intervention with the greatest net benefit would be considered the most efficient. For the model- and trial-based analyses, probabilistic, or stochastic (for the trial based analysis), along with deterministic sensitivity analyses, will be constructed.

### Sample size and feasibility

#### Sample size sought

A sample size of n =338 per group is required to provide 90% power to detect a difference in the mean area under the curve (AUC) of 0.25 standard deviations derived from EQ-5D score measurements, with a significance level of 5% (two-sided alpha). Good data on 24-months AUC for this instrument in this patient group is sparse, but a 0.25 effect size has often been shown to correspond to a worthwhile difference in quality of life measures. This would equate to a difference of 0.1 in the AUC (QALY) assuming a standard deviation of 0.4. Evidence-based strategies will be used to enhance questionnaire response rates in this highly motivated group of patients. Conservatively, to allow for 15% non-response in the outcome, it is proposed to randomise 400 subjects in each of the two groups. Such a sample size would provide 90% power to assess differences in the secondary outcome of recurrence between the two surgical techniques from around 10% to around 4%. This magnitude of difference is supported by a recent systematic review which showed a non-statistical trend higher recurrence in the SH group compared to TH group [4].

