#### Secondary

The patient-reported outcomes include the following:generic health profile measured by SF-36 and EQ-5D,visual analogue scale (VAS) pain score,Cleveland incontinence score,haemorrhoid symptom score,post-operative analgesia consumption,recurrence of haemorrhoids, andtenesmus.

Clinical outcomes are perioperative and postoperative complications including the following:haemorrhage,requirement for blood transfusion,anal stenosis,anal fissure,urinary retention (which requires catheterisation),residual anal skin tags,difficult defecation,wound discharge,pelvic sepsis, andpruritus.

Economic outcomes will be the costs based on resource use data and include the following:Costs to the NHS and patients at two yearstime to recoverylength of hospital stayuse of health services for haemorrhoid related events or treatmentspatient costs (treatments, travel to health services, sick leave)need for alternative management for haemorrhoids (for example, surgery, drugs)other use of health servicesvisits to GP

ii. visits to practice nurse

iii. visits to colorectal surgeon2.Estimated lifetime cost to NHS and patient3.QALYs estimated from the EQ-5D at 24 months4.QALYs estimated over the patient’s lifetime5.Cost-effectiveness analysis (incremental cost per case of stapled haemorrhoidopexy and traditional haemorrhoidectomy excision avoided).

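### The 90% power stated for recurrence uses roughly the number randomised; after the plan's own 15% non-response it would be about 87%

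*Protocol article*

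**What the plan says.** All the figures are in the protocol article, Sample size sought. The primary outcome, the area under the EQ-5D curve, is given 338 per group for 90% power at a difference of 0.25 standard deviations. The number is then raised: "Conservatively, to allow for 15% non-response in the outcome, it is proposed to randomise 400 subjects in each of the two groups". The following sentence turns to recurrence: "Such a sample size would provide 90% power to assess differences in the secondary outcome of recurrence", with the rates going "from around 10% to around 4" per cent. No separate allowance for missing recurrence data is mentioned.

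Four other places bear on the point:

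- Measures of outcome, Secondary, lists recurrence among the patient-reported outcomes.
- Table 1 collects recurrence by post or web at 12, 24 and 60 months. Routine hospital records are added at 12 and 60 months but not at 24.
- Data collection and processing places the main outcome assessment after completion of the 24-month follow-up.
- Flagging on central medical databases describes flagging participants in routine records for further haemorrhoidal surgery, at 12 and 60 months.

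The test level comes from Ground rules for the statistical analysis: "Statistical significance will be at the two-sided 5% level with corresponding confidence intervals derived".

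**The concern.** Two consecutive power statements appear to use different denominators without saying so. The primary figure counts participants with data, and the recurrence figure seems to count everyone randomised. If recurrence suffers the same non-response as the questionnaire on which it is reported, the stated 90% is somewhat higher than the design gives.

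Recurrence is the only secondary outcome for which the article quotes a power. The Background also presents recurrence and re-intervention as the longer-term drawback of the stapled operation, set against less early pain. Readers may therefore use the stated power when they interpret a recurrence comparison that is not significant.

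**Working it through.** **Inputs**
- Two-sided 5% level (Sample size sought; Ground rules for the statistical analysis).
- Recurrence 10% v 4%, 400 randomised per group, 15% non-response, 338 per group for the primary outcome (Sample size sought).
- Equal allocation (Randomisation and allocation).
- Assumption: the 15% applies to recurrence as well, which leaves 400 × 0.85 = 340 per group.

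**Step 1: the primary calculation.** n = 2(1.960 + 1.2816)² / 0.25² = 336.2, so 337 against the stated 338. Power at 338 is 90.1%. Inflation: 338 / 0.85 = 397.6, so 398 against the stated 400. Both figures reproduce, and they confirm that 338 means participants with data.

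**Step 2: the formula for recurrence.** With difference d = 0.10 − 0.04 = 0.06 and mean proportion 0.07:
- null term: √(2 × 0.07 × 0.93) = √0.1302 = 0.3608
- alternative term: √(0.10 × 0.90 + 0.04 × 0.96) = √0.1284 = 0.3583
- power = Φ[(d√n − 1.960 × 0.3608) / 0.3583]

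**Step 3: the stated 90%.** At n = 400: (0.06 × 20 − 0.7072) / 0.3583 = 1.375, giving 91.5%. The stated figure therefore reproduces on the number randomised.

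**Step 4: the number with data that 90% needs.** n = (1.960 × 0.3608 + 1.2816 × 0.3583)² / 0.06² = (0.7072 + 0.4592)² / 0.0036 = 377.9, so 378 per group. The tolerable loss is (400 − 378) / 400 = 5.5%. At 15% loss, 378 / 0.85 = 444.7, so 445 per group would have to be randomised.

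**Step 5: power after 15% loss.** At n = 340: (0.06 × 18.439 − 0.7072) / 0.3583 = 1.114, giving 86.7%. At n = 338 it is 86.5%.

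**Step 6: dependence on the method.**

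| Two-sided method | 400 per group | 340 per group |
|---|---|---|
| Pooled normal approximation | 91.5% | 86.7% |
| Unpooled normal approximation | 91.8% | 87.0% |
| Exact enumeration, uncorrected chi-square | 92.5% | 88.0% |
| Arcsine | 92.6% | 88.1% |
| Likelihood ratio | 92.7% | 88.4% |
| Fisher exact | 90.5% | 84.5% |
| Continuity-corrected | 89.2% | 83.2% |

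No two-sided method reaches 90% at 340.

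**Step 7: dependence on the rates, at 340 per group (pooled).** 10% v 3.7% gives 90.4%, and 10.5% v 4% gives 90.6%. In the other direction, 9.5% v 4% gives 81.7%, and 10% v 4.5% gives 79.1%.

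**The case against.** The strongest reply has three parts.

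**The rates are approximate.** The article says around 10% and around 4%. A pair such as 10% v 3.7% still fits that description and restores 90% at 340 per group. This stands as a limit on the size of the point. It does not settle the matter, because equally small shifts the other way lower power by more than the shortfall in question.

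**The 15% may not be the loss for recurrence.** It is given for the outcome, in the context of questionnaire response for the EQ-5D, and is described as a conservative allowance. Routine-record flagging, and continued use of NHS records after withdrawal where the participant agrees, could recover some recurrences. This stands in part. However, Table 1 has no routine-data source for recurrence at 24 months, and the records identify further surgery, so they would miss recurrences managed without it.

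**The reference to sample size is ambiguous.** It could point to 400 or to 338. On the first reading the figure is correct for the number randomised, so the calculation itself is not wrong. On the second, power is 86.5%. Neither reading gives 90% once 15% are lost.

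A reader might infer that 90% holds only if all 400 per group respond. That is too strong, since 378 suffice. A reader might also infer that the trial is underpowered for its principal measure of durability. The documents do not support this either: recurrence is one of seven patient-reported secondary outcomes with no stated priority, and the primary sample size reproduces. Nor would three points of power materially mislead the interpretation of a null result, since confidence intervals are planned.

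**Conclusion.** The point holds as a minor one about the basis of a stated figure. The 90% matches roughly the 400 randomised per group and is valid with about 378 or more per group analysed. Under the plan's own 15% non-response, power for 10% v 4% is about 87% by the pooled approximation and 88% by exact enumeration, a shortfall of two to three points. At the stated effect the type II error is then about 13%, not 10%.

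This rests on two assumptions: that questionnaire non-response carries over to recurrence at 24 months, and that the rates are taken at their nominal values. If routine records kept the loss to about 5.5% or less, the stated 90% would stand.

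**What to change.** Replace the recurrence sentence with wording such as:

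> With 340 evaluable per group, power is about 87% for recurrence of 10% v 4%; 90% power is reached for 10% v about 3.7%, or with about 378 per group analysed.

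If the investigators expect routine records to reduce the loss for recurrence, they should say so and give the loss they assume.

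The cost is one sentence and a slightly less favourable figure. Recruitment, design and the primary calculation do not change.

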#### Recruitment rates

Previous experience of recruitment in NIHR/MRC surgery trials co-coordinated from the trial office, suggests that around 50% of those eligible will agree to be randomised. The recruitment period is anticipated to last 43 months (months 4 to 46 inclusive). Around 1,600 eligible patients are likely to have to be approached to randomise the required 800.

### Organisation

It is anticipated that there will be bi-annual PMG, six meetings of the TSC and five of the DMC. Two meetings are planned for collaborators (including the collaborating colorectal surgeons), the first timed to occur when all the centres have been identified and the second when results are available.

#### Local organisation in centres

##### Lead colorectal surgeon

Each collaborating centre will identify a lead colorectal surgeon (principal investigator (PI)) who will be the point of contact for that centre. The PI will take responsibility for ensuring that the outcome measures are taken consistently and in line with the standardised protocols developed for the study. Specifically, this person will do the following:accept overall responsibility for the eTHoS study locally;assist the eTHoS study office in establishing the study locally (for example agreement from clinical colleagues, helping the main study office to facilitate local trust approval, identify and appointing an RO and informing all relevant local staff about the study);identify eligible patients;explain the eTHoS study and take informed consent;take overall lead responsibility for ensuring that the outcome measures are taken consistently and in line with the standardised protocols developed for the study;take overall lead responsibility for all clinical aspects of the study locally (for example, if any particular concerns occur);notify the eTHoS study office of any unexpected clinical events which might be related to study participation;provide support and supervision for the local RO;represent the centre at the collaborators’ meeting;place patients who are randomised to SH or TH on the waiting list for surgery;complete fully the appropriate eTHoS paperwork for patient participation; andfacilitate/supervise/participate in the upload of this hardcopy patient data to the web based system.

##### Recruitment officer (RO) at each centre

Each collaborating centre will appoint a RO to organise the day to day running of the study in that centre. The overall responsibilities of this person will be as follow:work with the PI and other local colorectal surgeons in order to organise the day to day recruitment and follow-up of eTHoS participants of the study in that centre;keep regular contact with the PI and other colorectal surgeons, notifying them of any problem or unexpected development;maintain regular contact with the Study Office (including mailing of relevant material to the Study office);keep local staff informed of progress in the study;organise and supervise alternative recruiters in case of holiday or absence; andrepresent the centre at the collaborators’ meeting if required.

The specific responsibilities of this person will be as follows:Assist the PI and other local colorectal surgeons to keep a log of whether eligible participants are recruited or not (with reasons for non-participation)Assist the PI and other colorectal surgeons in the distribution of the Patient Information Sheet and the collection and organisation of the patient consent formsAs appropriate organise follow-up to consultation appointments at 6 weeks after surgery with eTHoS participantsEnsure timely processing of consent and patient data (complete on-line baseline and follow-up clinical-data collection forms and enter into web application)Undertake baseline measurements and follow-up measurements as appropriate and in accordance with eTHoS standard operating proceduresSupport completion (as appropriate) of research questionnaires with the patients both face to face (at baseline) and when required during follow-up, including over the telephone as indicated from the eTHoS Study Office (that is, in the case of non return or significant missing data)Act as a point of contact for the participants at all times and provide information about the trial, as necessary.

